Further, readmissions following sepsis or pneumonia are often preventable. Up to nearly half of readmissions after sepsis can be attributed to preventable causes and the preventability of readmission after pneumonia is recognized by the Centers for Medicare and Medicaid Services' (CMS) Hospital Readmission Reduction Program as an indicator of quality of care. Most patients hospitalized with sepsis or pneumonia are >65 years of age and have multimorbidity. Two-thirds of readmissions following sepsis or pneumonia were due to infection (~40%) and cardiovascular (15%) and respiratory disease (10%). In theory, adequately monitoring patients, detecting early signs of deterioration, and triaging them to appropriate care would decrease unnecessary care utilization and increase patient stability. This is the premise of several widespread interventions such as in-hospital rapid response teams, post-discharge remote patient monitoring (RPM) for heart failure, and primary care-led monitoring in the community.

However, there are critical gaps in knowledge regarding how comprehensively we should remotely monitor patient symptoms and types of health care teams best suited for responding to alerts to maximize patient time at home. The standard of care for patients with multimorbidity is to provide some level of care coordination or care provision after discharge, as we know it works. There is a large body of evidence demonstrating that post-acute care models as a whole reduce the risk of an individual returning to the hospital after discharge. Among these, more complex interventions that leverage multiple components and multiple care providers have greater effect on maintaining patients at home longer after discharge. Specific successful model components include care coordination/care management activities and patient self-management education.

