### 8.10. Analyses of heterogeneity of treatment effect

#### 8.10.1. Comparison group determination for heterogeneity of effect analysis

Because it is possible for our RAR design to reduce enrollment to under-performing arms, we may be at a power disadvantage for identifying heterogeneity of treatment effect (HTE) of each active intervention compared with STS as a function of baseline covariates: age, sex, race, chronic comorbidity index, comfort with technology, health literacy level, Area Deprivation Index, discharge location, illness severity and admitting diagnosis. Therefore, we may pool arms prior to HTE analysis based on arms' average effects. For instance, if both RPM-Low and RPM-High are on average effective, we will pool these patients. However, we may choose not to pool patients by care team component (Standard Team or Enhanced Team) since resource utilization for these components is different and stakeholders have expressed a strong interest in identifying subgroups that benefit, especially among those who receive the Enhanced Team component. Thus, all analyses described below will be repeated for comparisons between each active (and potentially pooled) intervention and STS arms.

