#### 8.10.2. Analysis of effect heterogeneity across pre-determined subgroups

We will conduct differential treatment effects analyses, comparing differences between RPM groups and STS across pre-specified subgroups of patient-level clinical, social, and environmental factors that could be potentially used to tailor service delivery. All analyses will be performed using a cumulative logit model for the primary PDHD outcome, including terms for treatment arm, subgroup, treatment by subgroup interactions, stratification variables, and calendar time of randomization. Subgroup variables and definitions were determined as plausibly related to treatment effect heterogeneity. Each subgroup variable will be analyzed in two ways: 1) four RPM arms kept separate; and 2) comparing standard team and enhanced team arms. Analyses will not be adjusted for multiple comparisons. Evidence of differential treatment effects across subgroup levels will be summarized using the posterior probability that interaction

terms are greater than 0. In addition, treatment effects by subgroup level will be summarized using the posterior median cumulative odds ratios from each model, and corresponding 95% credible intervals.

Subgroup definitions are as follows:

- Patient Age
  - <65 vs age ≥65
- Sex
  - Female vs male
- Race
  - White patients vs Black patients
- Chronic Condition index
  - CCI<5 vs CCI≥5
- Level of comfort with technology
  - Comfortable vs uncomfortable vs missing
- Health literacy level
  - Limited vs marginal vs adequate vs missing
- State-ranked Area Deprivation Index
  - Quartile 1 vs quartile 2 vs quartile 3 vs quartile 4 vs missing
- Location after discharge
  - Skilled Nursing Facility vs home
- Severity of illness
  - Severe (mechanical ventilation or vasopressor use during index hospitalization) vs not severe
- Discharge diagnosis
  - COVID vs Non-COVID Sepsis vs Other lower respiratory tract infection

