### 8.10.3. Analysis of effect heterogeneity on dichotomized outcomes

We will explore potential heterogeneity of the effects of active arms compared to control groups after dichotomizing the PDHD outcome, collapsing all values of PDHD less than 90 into a single category. This will facilitate the estimation of conditional average treatment effects on the risk difference scale.

For our first set of analyses, we will dichotomize continuous or ordinal covariates, and analyze the conditional absolute risk differences (cARD) between the levels of the dichotomized covariates. For each covariate, we will test the null hypothesis that there is no difference in the cARDs using the Q test. We will also calculate 95% CI for the cARDs and their differences.

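### The one-covariate-at-a-time heterogeneity analyses split age and the comorbidity index in two (8.10.3 also splits the Area Deprivation Index), which gives up information if benefit changes gradually; the size of the loss in this trial is unknown.

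*Combined protocol and SAP*

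**What the plan says.** Aim 2 is to find the patient subgroups for whom each care model works best. SAP section 8.10 approaches it in three ways.

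- **Section 8.10.2** fits a cumulative logit model to home days (PDHD), one subgroup variable at a time, with treatment-by-subgroup interactions. Age enters as below 65 against 65 or older, and comorbidity as "CCI<5 vs CCI≥5". ADI enters as "Quartile 1 vs quartile 2 vs quartile 3 vs quartile 4 vs missing", and health literacy keeps three levels plus missing. Results are posterior probabilities that interaction terms exceed zero, with subgroup odds ratios and credible intervals. No decision threshold is set.
- **Section 8.10.3, first set,** makes the outcome binary by "collapsing all values of PDHD less than 90 into a single category". For the covariates, "we will dichotomize continuous or ordinal covariates, and analyze the conditional absolute risk differences (cARD) between the levels of the dichotomized covariates". For each one, "we will test the null hypothesis that there is no difference in the cARDs using the Q test". The section gives no covariate cut-points and no significance level; the nearest indication is "We will also calculate 95% CI for the cARDs and their differences".
- **Section 8.10.3, second set,** builds multivariable prediction models (causal forest, R-learners, regularised regression), with no covariate splitting specified. It judges heterogeneity by one calibration slope.

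Section 8.10.1 concedes limited power for heterogeneity, which it attributes to adaptive randomization, and gives no figure.

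**The concern.** Age, CCI and ADI are available on a continuous or many-level scale. Splitting such a variable treats everyone on one side of the cut as alike. If benefit changes gradually with the variable, the contrast between the two groups carries less information than a slope would.

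In 8.10.3 the consequence is a less powerful Q test. In 8.10.2 it is a less precise estimate of effect modification for age and CCI. Either analysis could fail to show a real gradient, and a reported contrast at 65 or at 5 suggests a step in benefit that the data may not contain. This matters because power is already conceded to be short.

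Two features could add to it. The age cut may be uneven, since the protocol Background notes that "Most patients hospitalized with sepsis or pneumonia are >65 years of age". And for ADI and health literacy no two-level cut appears anywhere in the SAP, so the split used in 8.10.3 would be chosen later.

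**Working it through.** **Inputs from the documents.** Sample size 1,281 (protocol, Sample Size); 2.5% lost to follow-up and scenario 3 power of 0.851 at N=1500 (SAP 12.5, power calculations of 11/24/2023); 30% allocated to STS (SAP 8.7); probability of 90 home days 0.454 (SAP Table 2).

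**Assumptions, because the documents are silent.** Interaction size, covariate distribution, share of patients on each side of a cut, and a two-sided 5% level for the Q test (in line with the 95% intervals).

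**1. The plan's own figures.** The plan states no power for heterogeneity. Its nearest figures, main-effect power below N=1500, use an information-fraction approximation, the same device used below. Power(N) = Φ[(z(0.851) + 1.960)·√(N/1500) − 1.960]. At N=1250: Φ(3.001 × 0.913 − 1.960) = 0.782, as stated. N for 80% power: 1500 × (2.802/3.001)² = 1308, as stated.

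**2. Information kept by a split.** For a normal modifier with linear effect modification, cut at share p, the fraction kept is φ(z_p)²/[p(1−p)]. At 50/50 this is 0.159/0.25 = 0.637; at 75/25, 0.539; at 80/20, 0.0784/0.16 = 0.490. For a uniform modifier it is 3p(1−p), which is 0.75 at the median.

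**3. Power after the split.** Power = Φ[(1.960 + z(P))·√(fraction kept) − 1.960], where P is power on the continuous scale. For P = 80% at a median split: Φ(2.802 × 0.798 − 1.960) = 60.8%.

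| Modifier and split | Kept | from 90% | from 80% | from 50% | from 30% |
|---|---|---|---|---|---|
| Normal, 50/50 | 0.637 | 73.4% | 60.8% | 34.6% | 20.8% |
| Normal, 70/30 | 0.576 | 69.1% | 56.6% | 31.8% | 19.2% |
| Normal, 80/20 | 0.490 | 62.1% | 50.0% | 27.8% | 17.0% |
| Uniform, 50/50 | 0.750 | 80.2% | 67.9% | 39.6% | 23.7% |

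**4. At this trial's size.** 1,281 × 0.975 = 1,249 complete patients, of whom 30% is 375 on STS. Two pooled active arms at equal allocation hold half of the remaining 874, or 437. With a binary variance of about 0.25, the standard error of a change in risk difference per SD is 0.5 × √(1/375 + 1/437) = 0.0352. So 80% power needs 2.802 × 0.0352 = 0.099, or 9.9 percentage points per SD. For comparison, the plan's expected effect (OR 1.5) moves the probability of 90 home days from 0.454 to 0.555, or 10.1 points.

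| Change in risk difference per SD | Continuous | Median split | 80/20 split |
|---|---|---|---|
| 10 points | 81% | 62% | 51% |
| 7.5 points | 57% | 40% | 32% |
| 5 points | 30% | 21% | 17% |
| 2.5 points | 11% | 9% | 8% |

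**5. Simulation check.** 4,000 trials per setting, 375 against 437, probability of 90 home days 0.45, comparing a robust linear interaction with the two-group contrast (equivalent to the Q test for two groups). At 10 points per SD: 82% against 63% (median split), and 82% against 53% (80/20). At 5 points: 31% against 21% (median split). Type I error was about 5% for both.

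**6. The opposite case.** If the true effect is a step exactly at the cut, the split does better. Simulated power was 29% against 20%, 57% against 42%, and 82% against 64%, a gain of 8 to 19 points.

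**The case against.** Six points can be made for the plan.

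- **The loss is not a measured property of this trial.** It depends on an interaction size and a covariate shape that the documents do not give. This stands. To reach 80% power, one covariate must shift benefit by about the whole expected effect per SD. With smaller interactions every version of the test is weak, and the split costs fewer points.
- **Section 8.10.2 splits only age and CCI in two.** This stands. It also keeps home days ordinal.
- **Section 8.10.2 makes no accept-or-reject decision.** This stands. Talk of power and of a false negative applies to the Q test in 8.10.3; in 8.10.2 the cost is precision.
- **A reason is given.** Section 8.10.2 says that the subgroup definitions were chosen as plausibly related to effect heterogeneity and as factors that could guide service delivery. That supports showing results by these groups. It does not explain why the measured scale is left out.
- **The second set in 8.10.3 covers the gap.** In part. It specifies no splitting, repeats its random derivation and validation splits, and plots characteristics against predicted benefit. Its formal result is a joint one, so it does not replace a test for age or CCI.
- **The uneven age split is inferred.** This stands. The Background sentence describes such inpatients in general, not the enrolled patients, so the 70/30 and 80/20 figures are illustrations.

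**Conclusion.** The point holds as a minor, inexpensive improvement. The first set in 8.10.3 splits every continuous or ordinal covariate without stating cut-points, and 8.10.2 splits age and CCI, so neither is assessed singly on its measured scale. For a roughly normal modifier with linear effect modification, the information kept is about 64% at a median split and 49% at 80/20, which would take 80% power to about 61% or 50%.

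A reader might infer that Aim 2 as a whole loses 15 to 30 points of power. The documents do not support that. The range follows only for a normal, linear modifier, splits between 50/50 and 80/20, and starting power of about 50% to 90%. With starting power of 30% the loss is 9 to 13 points. For a uniform modifier at a median split it is 10 to 12 points (starting power 50% to 80%). With a step at the cut-point the split gains. Nor does the loss extend to ADI and literacy in 8.10.2, or to the multivariable models. The primary analysis is unaffected, and the separate splitting of home days at 90 is not challenged here.

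**What to change.** - **Section 8.10.3, first set:** for age, CCI and ADI, make the test a treatment-by-covariate interaction on the measured scale in a risk-difference regression. Use a linear term, with a 3-knot spline as a check.
- **Section 8.10.2:** add the same measured-scale interaction for age and CCI, and optionally ADI, to the cumulative logit model, and report its posterior probability.
- **Display:** keep the cut-points already stated for presenting subgroup estimates. For any covariate still split in 8.10.3, such as health literacy, write the cut into the SAP.

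The cost is SAP wording and a few model terms, using data already collected. The downside is the linearity assumption, which the spline checks.

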## 8.11. *Handling of missing data*

### 8.11.1. *Missing PDHD data*

The primary endpoint is ascertained using claims data for the majority of patients, and medical records review for the small subset of patients that either drop UPMC Health Plan coverage during the course of follow up, or are covered by the Medicare Fee-for-Service program. We will assume that no record of death or readmissions counted against the primary endpoint correctly correspond to the absence of these events for the patient, and therefore the primary outcome will be completely observed for all patients.

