## Sample Size

The study planned to enroll 1,668 patients across the five different arms (STS, RPM-Low + Standard Team, RPM-Low + Enhanced Team, RPM-High + Standard Team, and RPM-High + Enhanced Team). From this sample 1168 patients were expected to be discharged directly to home and 500 patients were expected to be discharged to SNF and then home. Accounting for an estimated 10% attrition, the final analytic sample size was expected to be 1,500.

However, in November 2023 it was decided to reduce the sample size to 1,281 due to recruitment challenges.

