## 2. DEFINITIONS

**Care team:** The individual or group of medical professionals whose role it is to screen RPM alerts and follow up with the patient, referring to the patient's PCP or other specialists if necessary.

**Home:** Level of residence or health care facility where the patient was residing prior to hospital admission.

**Heterogeneity of Treatment Effects (HTE):** The hypothetical scenario in which the effect of intervention on outcomes depends on baseline covariates.

**Index Hospitalization:** Hospitalization during which patient was enrolled in the clinical trial.

**Intention To Treat (ITT):** All eligible and consented patients who undergo randomization will be included in the ITT cohort for the purposes of analyzing the primary and secondary study outcomes.

**Intervention arms:** RPM-Low + Standard team, RPM-Low + Enhanced team, RPM-High + Standard team, RPM-High + Enhanced team.

**Remote Patient Monitoring (RPM):** An automatic electronic messaging system designed to push questions to patients at fixed intervals. Questions vary depending on the intensity of the RPM program (Low or High), but patient answers can trigger alerts and responses by members of the intervention care team.

**Study day:** The day of discharge to home is study day 0. The next calendar day is study day 1, etc.

**Study hospital:** Defined as the hospital where the patient was randomized and enrolled.

**Study withdrawal:** Defined as permanent withdrawal from study before completion of study activities. If a patient or surrogate requests withdrawal from the study, the clinician should seek explicit permission to continue data collection.

**Prognostic strata:** patient groups with different PDHD distributions.

**Predictive strata:** patient groups in which intervention effects are estimated individually.

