## 6. ENDPOINTS

### 6.1. Primary endpoint

The primary efficacy endpoint will be post-discharge home-days (PDHD) recorded over the first 90 days after discharge to the patient's home. Patients will be assigned -1 days if they die before day 90 post-discharge home. Among patients who survive 90 days or more, PDHD is recorded as the total number of days alive and out of acute care hospitals or post-acute care facilities (e.g., inpatient rehabilitation, skilled nursing facilities, long-term care facility). If a patient is readmitted to one of these facilities during the 90 days after returning home, then those days not at home will be subtracted from their PDHD. The following rules will be used to calculate PDHD.

- Home is defined as any location that does not involve insurance claims charged to UPMC Health Plan. This can include the patient's own residence, someone else's residence (family or friend), independent living facility or personal care home. It is not restricted to being the same location at which the patient resided pre-admission, so long as it does not involve UPMC Health Plan claims.
- The index hospitalization and post-acute health care facilities (e.g., long-term acute care facility, ventilator-rehabilitation unit, rehabilitation facility, transitional care units, skilled nursing care, nursing homes) visited following discharge are counted as "hospitals" until the patient is discharged home.
- PDHD can take on integer values from -1 to 90. Any calendar day partially spent in acute care hospitals or post-acute care facilities is counted as a full day for the purposes of calculating PDHD, regardless of whether it was part of the initial admission or any readmission.

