## 7. TRIAL CONDUCT

### 7.1. Data collection

Quantitative data will be collected from several sources. Self-report assessments will be gathered at baseline and 90 days post discharge using REDCap Cloud, a secure data collection platform. Clinical data, additional patient demographic/descriptive information, and health care utilization data will be extracted from electronic health records and payer claims at baseline and 90-days. These data collection procedures have been used previously by our site teams (e.g., successfully retaining over 80% of participants in other large-scale studies). For individuals who withdraw from the study, data will be retained up to the point of study withdrawal.

Qualitative telephone interviews will be conducted to understand patient or caregiver intervention-related experiences. We will conduct the interviews as soon as possible following the 90-day follow-up to maximize participants recall related to involvement in the study. We will conduct interviews with 120 patients (30 patients from each of the 4 intervention arms). If a patient is unable to participate in an interview due to medical complexity, we will attempt to interview his/her primary caregiver. All audio recordings of interviews will be transcribed by experienced qualitative researchers and de-identified. We will use a unique study ID to label all study materials related to participation with a tracking log as

the only link to identifying information. Transcripts will be stored on a secure cloud-based environment approved by UPMC.

We will use the NVivo 12 (QSR International, Australia) platform for data analysis. A constant comparative thematic content approach will be used to analyze the qualitative data. Our qualitative analysis will be iterative and will take place over the course of the qualitative data collection period. For example, we will review transcripts from the first few patient interviews to begin developing a codebook and to make needed modifications to our interview guide for subsequent interviews. A separate codebook will be developed for each interview type (i.e., patient, intervention providers, primary care physicians) with the input of the Co-Investigators and the Stakeholder Advisory Board. We will assess inter-rater reliability using percent agreement and kappa scores. Upon acceptable interrater reliability, the qualitative research team will thematically code all qualitative documents.

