| 13       | All Strong, Combo Additive   | 450                                                                | 106 | 132 | 134 | 678 | 1500  | 0.500/
0.007  | 0.778/0.004 | 0.801/0.002 | 1.000/
0.000 | 1.000/
0.000 | 0                  | 0     | 0     | 1     | -0.16 | 0.09  | 0.11  | -0.02 |

1084

1085

1086

1087

1088 Power Calculations 11/24/2023

1089 There is a possibility that full enrollment will not be feasible. In this section we illustrate the power that may be obtained in each of the scenarios above at  
 1090 sample sizes of 1200 to 1500 complete, with 1500 complete replicating the results shown above in the “with futility” tables. For the N=1500 column, taken  
 1091 from the table above, the results were computed via trial simulation. For the remaining columns, approximations were employed reflecting the information

fractions available at 1200 to 1450 complete patients. We expect these approximations to be close, but they are likely to be slightly aggressive, meaning that if they are off they are likely to overestimate power. We do not expect needed sample sizes to be off by more than ~25 patients.

Note that similar to the above tables, the table below shows sample sizes of complete patients. At present, the trial is observing 2.5% of patients lost to followup, significantly fewer than originally estimated. Nevertheless, to obtain a given number of complete patients, we must enroll a larger number. For example, to obtain 1350 complete patients with 2.5% loss to followup, we need to enroll  $1350/(1-0.025) = 1385$  patients total.

| Scenario        | N=1200 | N=1250 | N=1300 | N=1350 | N=1400 | N=1450 | N=1500 | N Needed for 80% power (if feasible) |
|-----------------|--------|--------|--------|--------|--------|--------|--------|--------------------------------------|
| 1, Null         | ~0.025 | ~0.025 | ~0.025 | ~0.025 | ~0.025 | ~0.025 | 0.023  | NA                                   |
| 2, One Weak     | 0.256  | 0.265  | 0.274  | 0.282  | 0.291  | 0.299  | 0.308  | NA                                   |
| 3, One Expected | 0.765  | 0.782  | 0.798  | 0.812  | 0.826  | 0.839  | 0.851  | 1308                                 |
| 4, One Strong   | 0.963  | 0.969  | 0.974  | 0.978  | 0.981  | 0.984  | 0.987  | <1000                                |
| 5, Two Weak     | 0.347  | 0.359  | 0.371  | 0.382  | 0.394  | 0.406  | 0.417  | NA                                   |

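### The SAP declares the primary outcome completely observed and, read literally, counts time after withdrawal or loss to follow-up as event-free time at home

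*Combined protocol and SAP*

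**What the plan says.** The SAP is section 8 of the Domain-Specific Appendix (DSA).

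- **Rule for absent records (DSA 8.11.1).** PDHD comes from claims for most patients, and from records review for those with lapsed coverage or Medicare fee-for-service. Then: "We will assume that no record of death or readmissions counted against the primary endpoint correctly correspond to the absence of these events", and "therefore the primary outcome will be completely observed for all patients".
- **Scoring (DSA 6.1).** "PDHD can take on integer values from -1 to 90", with -1 for death. "Home is defined as any location that does not involve insurance claims charged to UPMC Health Plan", so a day without such a claim defaults to home.
- **Withdrawal (DSA 7.1; the protocol's Data Collection section agrees).** "For individuals who withdraw from the study, data will be retained up to the point of study withdrawal".
- **Analysis set (DSA section 2).** "All eligible and consented patients who undergo randomization will be included in the ITT cohort".
- **Loss.** The protocol's Sample Size section planned 1,668 patients to analyse 1,500: "Accounting for an estimated 10% attrition". The power calculations of 11/24/2023 in DSA 12.5 say: "At present, the trial is observing 2.5% of patients lost to followup, significantly fewer than originally estimated". They enlarge enrollment to reach a target number of complete patients.
- **What covers missing data.** Multiple imputation in 8.11.2 is for secondary endpoints and baseline covariates. Section 8.9.8 repeats the analysis in health-plan members covered for all 90 days. The simulations in 12.2 assume no dropout.

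**The concern.** The outcome cannot be complete for every patient while some patients are lost and withdrawn patients' data end early. Sections 8.11.1 and 6.1 together turn the unobserved part of follow-up into days at home. Suppose a patient withdraws on day 5 with no event and dies on day 40, and the death is not on record. The literal rule gives 90 instead of -1, the best score in place of the worst.

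If loss is equal across arms and there is no effect, the error cancels. If loss differs, the comparison tilts toward the arm that loses more patients. The success threshold of 0.991 was calibrated in simulations without dropout, so nothing in the plan shows how it behaves under this rule. Section 8.9.8 excludes fee-for-service and lapsed-coverage patients but keeps insured members who withdrew.

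The protocol's Sample Size section and DSA 12.5 point the other way: they do not count lost patients as complete. Scoring them as event-free and leaving them out are two different primary analyses, and the plan does not choose between them.

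**Working it through.** **1. The plan's own figures.** DSA 12.5: 1350/(1 - 0.025) = 1384.6, stated as 1385. Protocol: 1668 x 0.90 = 1501, stated as 1,500. Both reproduce, and both treat lost patients as not complete.

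**2. Inputs.**
- N = 1,281 (protocol, Sample Size), with 30% to STS and 70% over four RPM arms (DSA 8.7). An equal split is assumed: 384 STS and 1281 x 0.70/4 = 224 per RPM arm.
- PDHD distribution: DSA Table 2 (13.3% deaths, 45.4% at 90; it sums to 0.999 and was rescaled). It was used alone, and also mixed over strata as in DSA 12.2 (11% severe, OR 0.75; 37% SNF, OR 0.35). The mixture has 20.2% deaths and 36.3% at 90.
- Total loss 2.5%: 0.025 x 1281 = 32 patients.
- Threshold 0.991, one-sided z = 2.366, nominal per-arm false success 0.009.

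**3. Assumptions not in the documents.** The split of loss by arm; every lost patient scored 90, which is an upper bound because events recorded before loss still count; lost patients otherwise like the rest; true OR = 1.

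**4. Loss splits that keep the total at 2.5%.**
- Equal: 2.5% in each arm.
- RPM twice STS: 0.30x + 0.70(2x) = 1.7x = 0.025, so STS 1.47% and RPM 2.94%.
- All in RPM: 0.025/0.70 = 3.57%, STS 0%.
- All in STS: 0.025/0.30 = 8.33%, RPM 0%.

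**5. Formulas.** Move share d of an arm's distribution to 90 and fit a two-arm proportional-odds model to the expected counts, giving the apparent log OR b. Whitehead's variance is 3/(1 - sum of cubed mean cell probabilities) x (1/384 + 1/224). For the mixture this is about 3.23 x 0.00707 = 0.0228, SE 0.151. For Table 2 alone it is about 3.39 x 0.00707 = 0.0240, SE 0.155. Per-arm false success = Phi(-2.366 + b/SE).

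**6. Results, one RPM arm against STS.**

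| Split of the 2.5% | OR, Table 2 alone | False success | OR, strata mixture | False success |
|---|---|---|---|---|
| Equal | 1.00 | 0.9% | 1.00 | 0.9% |
| RPM twice STS | 1.03 | 1.4% | 1.03 | 1.5% |
| All in RPM | 1.07 | 2.6% | 1.08 | 3.0% |
| All in STS | 0.86 | <0.1% | 0.84 | <0.1% |

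Example (mixture, RPM twice STS): b = 0.0303; 0.0303/0.151 = 0.20; Phi(-2.366 + 0.20) = 0.015. For all loss in RPM: b = 0.0736; 0.0736/0.151 = 0.49; Phi(-1.88) = 0.030.

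**7. Limits.** This is a large-sample frequentist approximation without adaptive randomization, interim analyses or time buckets. The figures are per arm. Success needs only one arm to pass (8.9.1), so the trial-level figure would be higher; it is not computed here.

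**The case against.** **The text does not name withdrawals.** Section 8.11.1 describes passive ascertainment and mentions neither withdrawal nor loss. Section 8.6 uses patients whose PDHD has been recorded, and 12.5 counts complete patients, so lost patients might simply be left out. This stands in part: the day-5 example follows from combining 8.11.1, 6.1, 7.1 and the ITT definition and is not a stated rule. But 8.11.1 speaks of all patients, and a plan that permits both readings needs correcting.

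**Exposure may be below 2.5%.** The term lost to follow-up is not defined. The protocol's measures table lists EHR, health information exchange and participant report beside claims, so a missed survey need not mean missing PDHD. DSA section 2 asks clinicians to seek permission to go on collecting data after withdrawal. The DSMB sees reports on missingness. All of this stands and could shrink the problem, but the plan gives no count.

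**Section 8.9.8 helps.** It does, for lapsed-coverage and fee-for-service patients only.

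**Two stronger readings are tempting and not supported.**
- *RPM arms lose more patients because they are more burdensome.* No loss by arm is given. Stopping RPM is not study withdrawal: the protocol lets participants stop the program, and non-responders keep receiving invitations.
- *Events are found more fully in RPM arms because call-center staff review non-responders' charts.* That review decides whom to contact. Nothing says it feeds PDHD, whose stated sources do not differ by arm.

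**Conclusion.** The point holds. Section 8.11.1 contradicts the plan's own handling of withdrawal and loss. Followed literally, it scores unobserved time as time at home, which favors the arm with more loss, and no planned analysis covers insured members who withdraw.

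The size is conditional. At 2.5% total loss with every lost patient scored 90 and no true effect, the apparent OR runs from 1.00 (equal loss), through about 1.03 with per-arm false success about 1.5% (RPM loss twice STS), to 1.07 to 1.08 with about 3% (all loss in RPM). Loss concentrated in STS would instead hide benefit. These splits are assumptions. A reader might infer that the trial's result is already biased toward RPM; the documents do not show that, because loss by arm is not reported.

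**What to change.** 1. Delete the statement in 8.11.1 that the outcome is completely observed for all patients. Reconcile it with the protocol's Sample Size section and the 12.5 power calculations, and define withdrawal and loss to follow-up.
2. For each patient, define the last date to which facility use and vital status are known from claims, EHR or health information exchange. It should not run past withdrawal unless continued collection was permitted.
3. If that date falls before day 90, treat PDHD as incomplete, not event-free. Multiply impute the remaining days and vital status given arm, strata and observed course. Admissible values are -1, or from the home days already accrued up to 90 minus the days already lost. For example, a patient at home throughout the first 60 days can end only at -1 or 60 to 90.
4. Add an arm-specific delta or tipping-point sensitivity analysis for these patients.
5. Report withdrawal and loss by arm.

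A likelihood that only sums the cells from -1 to 90 minus days lost is not a substitute. It admits values that accrued home days rule out. It also gives a withdrawn patient without events a contribution of 1, in effect deleting that patient while those with earlier events still count.

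The cost is a little more analysis work and slightly wider intervals.
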